#### Secondary outcomes

2.9.2

The secondary outcomes included the percentage of hematoma enlargement after taking the drug. After taking the medicine, participants will undergo 4 follow-up CT scans to collect information about the effect of the ABRS method on hematoma absorption or enlargement. Other secondary outcomes include the Barthel index (BI), National Institutes of Health stroke scale (NIHSS) score, mortality rate, all-cause mortality rate, TCM stroke syndrome evaluation scale, and adverse events.

### Safety assessment

2.10

Safety will be evaluated according to the incidence of adverse events and the results of clinical laboratory examinations. All adverse events will be recorded. The possible association between adverse events and the intervention will be determined according to a 5-level classification: affirmative, probable, possible, suspicious, and impossible.

Any adverse events during the trial will be recorded using the “adverse event form” and continue to be investigated. Researchers will record the treatment process if needed and results until the laboratory examination results return to normal and symptoms and signs disappear. All SAEs will be reported to the research ethics committee within 24 hours. When participants become unsuitable to continue the trial due to adverse events, they will be withdrawn from the trial immediately.

Clinical laboratory examinations will include routine blood, urine, stool + occult blood, liver function, kidney function, coagulation function, glucose and D-dimer tests, and electrocardiography.

### Data collection and management

2.11

The trial uses the CRF to collect on the day of enrollment, at 24 ± 2 hours, 48 ± 2 hours, and 72 ± 2 hours after taking the medicine, 14 ± 2 days after onset. The 2 follow-up visits were carried out at 3 months ± 7 days and 6 months ± 7 days after onset. More information about the study visits is shown in Table 1.

**Table 1 T1:** Study schedule.

		After taking the medicine				Follow-up	
Assessments	Enrollment	24 h	48 h	72 h	14 days after onset	3 months after onset	6 months after onset
Informed consent	×						
Randomization	×						
Medical history	×						
Physical examination	×				×		
General demography	×						
CT scan	×	×	×	×	×		
TCM stroke syndrome evaluation scale	×				×	×	×
NIHSS	×				×		
BI	×				×	×	×
mRS	×					×	×
Routine blood test	×				×		
Routine urine test	×				×		
Routine stool + occult blood test	×				×		
Liver and kidney function tests	×				×		
Coagulation function and D-dimer tests	×				×		
Glucose test	×				×		
Electrocardiography	×				×		
Distribution of drugs	×						
Recovery after drug use					×		
Recording of combined medications	×				×		
Recording of adverse events	×				×		
Safety assessment					×	×	
mortality					×	×	×

BI = Barthel index, mRS = modified Rankin scale, NIHSS = National Institutes of Health stroke scale, TCM = traditional Chinese medicine.

The participant's name, medical records, and data collected relating to the study will remain confidential information. Participants will be identified for the purposes of the study by initials and an assigned participant number. To ensure the security of the data, study-related information will be stored in a locked file cabinet in a safe place that cannot be accessed without permission.

To ensure the authenticity, accuracy, and completeness of the data, the quality of the data will be reviewed on site by a monitor through 100% source data verification. Errors will be submitted to the researchers for correction. After the observation course of the participant, the researcher submitted the CRF, informed consent, and medication record of the participant to the main researchers of their recruiting centers for review within 3 working days and submitted these study files to the project leader for review within 1 week.

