### Study design and setting

2.1

The study is a multicenter, prospective, randomized, double-blind, placebo-controlled clinical trial. Participants will be randomly assigned to the activating blood and removing stasis (ABRS) granule group or placebo group. Group allocation ratio is 1:1. The patients were stratified according to the time of enrollment. Patients who enrol within 24 to 48 hours after onset will enter strata A, and patients who enrol within 49 to 72 hours (including 48–49 hours) after onset will enter strata B. The strata sample size ratio is 1:1. Participants will receive ABRS granules in addition to routine treatment or placebo in addition to routine treatment. The treatment cycle is 14 days. The primary outcome is disability degree (modified Rankin scale score). This study is reported in accordance with the Standard Protocol Items: Recommendations for Interventional Trial (SPIRIT) guidelines.^[13]^ The study flow chart is shown in Fig. 1.

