### Study objectives

2.2

The objective is to investigate the efficacy and safety of the ABRS method for acute cerebral hemorrhage and to determine the optimal intervention time.

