#### Inclusion criteria

2.3.1

1.Diagnosis with cerebral hemorrhagic stroke confirmed by computed tomography (CT).2.Age between 35 and 80 years old.3.Stroke onset time within 24 to 72 hours.4.Receive conservative medical treatment.5.Glasgow coma score >6 points.6.mRS score before onset of 0 to 1 point.7.Informed consented.

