### Intervention

2.7

In addition to routine treatment (including general treatment, control of blood pressure, reduced intracranial pressure, and so on) according to the guidelines, participants will immediately receive ABRS granules or placebo after randomization. The preferred method of intervention will be oral; if the patient cannot swallow normally, the drug will be given nasally. The dosage will be 1 packet (15 g) twice a day for 14 days. The ABRS granule or placebo will be completely dissolved in 150 mL of boiling water before administration. The ABRS granule contains 8 kinds of herbs. The placebo was made from 5% ABRS granule and dextrin. The ABRS granules and placebo were produced and packed by China Resources Sanjiu Medical and Pharmaceutical Co., Ltd., Shenzhen, China, and passed the quality inspection before leaving the factory. The researchers have completed unified training and will patiently communicate with participants to increase compliance. Participants with <80% medication compliance will be excluded.

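### Drug return and the only scheduled post-baseline laboratory tests and ECG are timed 14 days from onset, before the 14-day course started at 24–72 hours can finish

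*Protocol article*

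**What the plan says.** Patients enter on "Stroke onset time within 24 to 72 hours" (section 2.3.1). Under section 2.7, "participants will immediately receive ABRS granules or placebo after randomization", and the regimen reads: "The dosage will be 1 packet (15 g) twice a day for 14 days". Section 2.1 repeats the length: "The treatment cycle is 14 days".

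Section 2.1 also splits patients by enrollment time. Stratum A covers 24–48 hours; for the later stratum, "patients who enrol within 49 to 72 hours (including 48–49 hours) after onset will enter strata B". One objective in section 2.2 is "to determine the optimal intervention time".

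Section 2.11 counts the early visits from first dose but the next one from onset: "72 ± 2 hours after taking the medicine, 14 ± 2 days after onset". In Table 1 this onset-timed visit carries the row "Recovery after drug use" and every post-enrollment mark for blood, urine, stool, liver, kidney, coagulation, D-dimer and glucose tests and ECG. The next visit is at 3 months. It has a general safety-assessment mark but no laboratory test or ECG.

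**The concern.** The dosing rule and the visit rule run on different clocks. No one starts drug before day 1 after onset, so a 14-day course cannot be over at day 14. A site following the schedule has two options, and each has a cost.

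- **Collect the drug at the visit.** Treatment is then cut short, and more so for late starters. The strata would differ in treatment length as well as in start time, which blurs any comparison across strata meant to identify the best time to intervene.
- **Leave the drug with the patient.** No later drug return is scheduled, and the laboratory results on which section 2.10 partly bases safety miss the last days of exposure.

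Sites may also choose differently from one another. A further, conditional issue is the 80% compliance rule in section 2.7: if packets were counted at this visit against the full 28, a fully adherent patient could appear non-compliant.

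**Working it through.** The plan states no end-of-treatment day to reproduce, so this is timeline arithmetic.

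**Inputs.** Start time *s* is 24–72 h after onset (sections 2.3.1 and 2.7). In stratum A, *s* = 24–48 h; in stratum B, *s* is above 48 and up to 72 h (section 2.1). The course is 2 × 14 = 28 packets (section 2.7). The visit is at 14 ± 2 days after onset, that is 288–384 h with nominal 336 h (section 2.11).

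**Assumptions.** Dosing is every 12 h from the first dose. For the averages, start times are uniform within stratum; for the window shares, visits are uniform over days 12–16.

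**End of treatment.** Last packet = *s* + 27 × 12 h = *s* + 324 h. Course end = *s* + 336 h.

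| Start (h) | Last packet (day) | Course end (day) | Days on drug at day 14 | Days on drug at day 12 |
|---|---|---|---|---|
| 24 | 14.5 | 15.0 | 13.0 | 11.0 |
| 48 | 15.5 | 16.0 | 12.0 | 10.0 |
| 60 | 16.0 | 16.5 | 11.5 | 9.5 |
| 72 | 16.5 | 17.0 | 11.0 | 9.0 |

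At the nominal visit the last packet is still 14.5 − 14 = 0.5 to 16.5 − 14 = 2.5 days away.

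**Packets taken by visit hour *v* under full adherence.** The count is ceil((*v* − *s*)/12) if a dose due at the visit hour is excluded, or floor((*v* − *s*)/12) + 1 if it is included, capped at 28. The ranges below cover both.

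| Visit day | Stratum A | Stratum B |
|---|---|---|
| 12 | 20–23 | 18–20 |
| 13 | 22–25 | 20–22 |
| 14 | 24–27 | 22–24 |
| 15 | 26–28 | 24–26 |
| 16 | 28 | 26–28 |

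**Packets left at day 14.** Stratum A has 1–4 left, mean (2 + 3)/2 = 2.5, which is 2.5/28 = 9% of the course. Stratum B has 4–6 left, mean (4 + 5)/2 = 4.5, or 16%. The difference is 2 packets, or 1 day.

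**Share of the window before the last packet.** This is min(1, (*s* + 324 − 288)/96) = min(1, (*s* + 36)/96). It is 62.5% for a 24 h start, 87.5% at 48 h and 100% from 60 h. The stratum A mean is (0.625 + 0.875)/2 = 75%. In stratum B the first half averages (0.875 + 1)/2 = 0.9375 and the second half is 1, so the mean is (0.9375 + 1)/2 = 97%.

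**Compliance, only if counted at this visit out of 28.** 80% of 28 is 22.4, so 23 packets are needed. Stratum B reaches at most 20/28 (71%) at day 12 and 22/28 (79%) at day 13. Stratum A is below 80% at day 12, except possibly an exact 24 h starter. At day 14 only an exact 72 h starter is borderline, and at days 15–16 nobody is below.

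**The case against.** The window takes up much of the mismatch. By day 16 all of stratum A, and those in stratum B who started by about 60 h, have taken the last packet; later starters have only 1–2 packets left. Sites could book late, and the 75% and 97% figures assume evenly spread visits, for which the protocol gives no basis. This stands as a limit on size. It does not remove the conflict at the nominal day, and after a start later than 60 h both rules cannot be met.

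The Table 1 row speaks of recovery after use, and two sections fix 14 days of treatment, so staff may well not take packets away mid-course. That is fair, and early collection is a possibility rather than a certainty. But if drug is left with the patient, the gap in drug return and laboratory cover follows.

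Section 2.10 records all adverse events during the trial and follows abnormal results until they are normal, and Table 1 marks a safety assessment at 3 months. Clinical events therefore have a reporting route. An abnormal laboratory value first arising after this visit does not, because no later test is scheduled.

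The compliance point is the weakest. The article gives no formula, and section 2.11 mentions a medication record that could be counted later. It stands only as a conditional risk.

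Finally, a condensed article may leave visit procedures to a fuller protocol. Here, though, both rules are stated, and they disagree.

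**Conclusion.** The concern holds. A 14-day course begun 24–72 h after onset ends at day 15–17, while drug return and the only scheduled post-baseline laboratory tests and ECG sit at day 14 ± 2. At the nominal visit nobody has finished, and the shortfall averages 2.5 packets in stratum A and 4.5 in stratum B. The course end follows from the stated dates alone. The packet counts and the timing of the last packet also rest on 12-hourly dosing, the averages on uniform starts, and the window shares additionally on evenly spread visits.

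The consequences are bounded. Randomization is 1:1 within strata, so the comparison of ABRS with placebo is not biased by this, and the 6-month mRS and the sample size are untouched. What is affected is end-of-treatment safety cover, drug accountability and, if drug is collected early, equality of treatment length between the timing strata. It should be corrected, but it does not threaten the main result.

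**What to change.** Tie drug recovery, the compliance assessment, laboratory tests, ECG and this visit's combined-medication and adverse event entries to 14 days after first dose, with a window of +2 days and no early side. Since the last packet falls 13.5 days after first dose, every course is then complete; the nominal visit lands at day 15–17 after onset. Define compliance as packets taken divided by packets due. NIHSS and CT may stay timed from onset, and dosing does not change.

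The cost is a visit-window amendment and a CRF line. The downside is that part of the visit moves 1–3 days later than NIHSS and CT, which may need a second contact.

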### Sample size

2.12

The sample size was calculated by PASS software version 15 (Kaysville, UT). In a previous study, the rate of unfavorable disability (according to the mRS score) in the control group was 56%.^[15]^ We assume that the rate of unfavorable disability (according to the mRS score) in the treatment group will be 36%, that is, decreased by 20%. After a 2-sided Z test, PASS software calculated that the sample size of each group should be 129. Considering a 20% dropout rate, 312 patients will need to be enrolled.

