### Statistical analysis

2.13

Inferential statistical analyses as specified will be conducted, and all comparisons will be between the ABRS granule group and the placebo group. The statistical analyst will be blinded to the participants’ personal information and group assignment during the trial. The primary analysis will be based on the full dataset following the intention-to-treat analysis principle for all efficacy outcomes, while the secondary analysis will be based on the per protocol dataset. For the analysis of safety outcomes, a safety dataset will be used. The primary outcome will be determined by a comparison of the changes in the patients’ mRS scores between the 2 groups at 6 months after onset. The secondary outcomes will include the mortality rate, hematoma enlargement percentage, all-cause mortality rate, adverse events, TCM stroke syndrome evaluation scale score, BI, and NIHSS score. The hematoma enlargement percentage will be measured at baseline, 24, 48, and 72 hours after taking the medicine and 14 days after onset. The mortality rate, all-cause mortality rate, BI, and TCM stroke syndrome evaluation scale score will be measured at 14 days, 3 months, and 6 months after onset. The NIHSS score will be measured at 14 days after onset. The mRS score will be measured at 3 and 6 months after onset.

Missing data regarding the primary and secondary outcomes will be imputed using the last observation carried forward (LOCF) method. Independent *t* tests or Wilcoxon rank-sum tests will be used to analyze continuous outcomes. Chi-squared tests will be used to analyze categorical data. Analysis of variance or a generalized linear mixed model will be used for repeated measurement data. Regarding mortality, survival probabilities will be estimated using the Kaplan–Meier method. Two-sided 95% confidence intervals will be constructed for assessment, and a 2-sided alpha level of 0.05 will be used to indicate significance. Adjustments will be made for baseline imbalances. Descriptive statistics, including the number and percentage for categorical variables and the number, mean, standard deviation, median, minimum and maximum for continuous variables, will be provided. Listings of individual patient data will also be produced. A comprehensive statistical plan will be prepared and finalized prior to unblinding and analysis of the data.

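### Enrolling 312 does not cover 20% dropout: it leaves about 125 per group, not the 129 the protocol requires

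*Protocol article*

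**What the plan says.** The calculation is in section 2.12 (Sample size) of the protocol article. It cites a previous study in which "the rate of unfavorable disability (according to the mRS score) in the control group was 56"% and assumes that the rate "in the treatment group will be 36%, that is, decreased by 20"%, an absolute difference of 20 percentage points. The test is a two-sided Z test, and the result is that "PASS software calculated that the sample size of each group should be 129". The next sentence inflates for loss: "Considering a 20% dropout rate, 312 patients will need to be enrolled".

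Section 2.1 fixes equal allocation ("Group allocation ratio is 1:1"), so 312 means 156 per group. Section 2.13 gives the significance level: "a 2-sided alpha level of 0.05 will be used to indicate significance". The abstract repeats the total of 312. Section 2.12 states neither the power nor the inflation formula.

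**The concern.** The dropout allowance exists so that the required number remains after the assumed loss. To keep n patients after a proportion d is lost, one enrols n/(1 − d). The figure of 312 is too low for this and lies near n × (1 + d), a common slip that always under-inflates.

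A reader of section 2.12 will conclude that 129 per group is secure at 20% dropout. If it is not, the section misstates how much loss the trial can absorb, and the power behind the 129 is not what the trial has under its own dropout assumption.

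**Working it through.** **Inputs**

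| Quantity | Value | Source |
|---|---|---|
| Unfavourable outcome, control | 56% | section 2.12 |
| Unfavourable outcome, treatment | 36% | section 2.12 |
| Test | two-sided Z | section 2.12 |
| Alpha | 0.05, two-sided | section 2.13 |
| Allocation | 1:1 | section 2.1 |
| Required per group | 129 (258 in total) | section 2.12 |
| Dropout | 20% | section 2.12 |
| Enrolled | 312 (156 per group) | section 2.12, abstract |
| Power | not stated; inferred in step 1 | – |

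**Step 1. Reproduce the 129.** With pooled variance under the null hypothesis and no continuity correction,

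n = [z(0.975) × √(2p̄(1 − p̄)) + z(power) × √(p₁(1 − p₁) + p₂(1 − p₂))]² / (p₁ − p₂)²,

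where p₁ = 0.56, p₂ = 0.36 and p̄ = 0.46. At 90% power:

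- first term: 1.960 × √0.4968 = 1.3815
- second term: 1.2816 × √0.4768 = 0.8849
- n = (2.2664)² / 0.04 = 128.4, rounded up to 129

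This matches the protocol. The same formula gives 97 at 80% power, 110 at 85% and 159 at 95%, so 90% is the only one of these usual values that returns 129. At 90% power the unpooled version gives 126 and the continuity-corrected version 139. Pooled variance and 90% power are therefore well-supported inferences, but they are not stated in the document.

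**Step 2. Check the inflation.** This step needs only the printed 129, 20% and 312.

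- Remaining after 20% loss: 312 × 0.80 = 249.6, or 124.8 per group
- Shortfall: 129 − 124.8 = 4.2 per group, or 258 − 249.6 = 8.4 in total
- Enrolment needed: 258/0.80 = 322.5, so 323 in total; per group 129/0.80 = 161.25, so 162, which makes 324
- Largest dropout that 312 can absorb: 1 − 258/312 = 17.3%

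**Step 3. Where 312 may come from.** Multiplying gives 258 × 1.2 = 309.6. Per group, 129 × 1.2 = 154.8, which rounds up to 155 and makes 310. The next multiple of four (two arms by two time strata) is 312. The document does not explain the rounding, so this route is a guess. The shortfall does not depend on it, because no upward rounding takes 322.5 to 312.

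**Step 4. Effect on power.** Using the formula of step 1, power = Φ[(0.20 × √n − 1.3815)/0.6905], where 0.6905 = √0.4768:

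| Patients per group | Power, 56% vs 36% |
|---|---|
| 129 (stated requirement) | 90.1% |
| 125 (312 enrolled, 20% lost) | 89.2% |
| 124 | 89.0% |
| 156 (all enrolled counted) | 94.7% |
| 162 (324 enrolled, all counted) | 95.4% |

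**The case against.** There are three fair points on the other side.

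- **The primary analysis does not drop anyone.** Section 2.13 specifies intention-to-treat with last observation carried forward. Nominally all 156 per group are analysed, and the formula then gives 94.7% power. This matters for wording: 125 per group describes patients with an observed six-month score, not the primary analysis set. It does not rescue the arithmetic. Section 2.12 itself treats dropout as a loss to be made up; if dropouts counted in full, no inflation would be needed. Carrying forward a three-month or enrolment mRS, the only earlier values in Table 1, does not restore a missing six-month outcome.
- **The effect is negligible.** A loss of about 0.9 percentage points of power is smaller than the uncertainty in the assumed 56% and 36%. This stands. The finding is a misstatement to correct, not evidence of an underpowered trial.
- **The power figures rest on inference.** This also stands. Neither 90% power nor the pooled form is printed. The mismatch between 129, 20% and 312 needs neither.

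That a journal article condenses the full protocol is no defence here. Nothing is claimed to be missing: the three figures are printed together and disagree.

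**Conclusion.** The statement is wrong as written. With equal groups, 129 per group, 20% dropout and 312 enrolled cannot all hold. The enrolment is 12 short of the 324 that 20% dropout requires (11 short of 323 if the total is inflated directly), and it covers 17.3% dropout at most.

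That conclusion rests only on printed figures. The size of the consequence, 89.2% power against 90.1%, rests also on the inferred pooled Z test and on counting only patients with an observed six-month outcome. The practical effect is small, but the sample size justification should be correct, so it should be amended.

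**What to change.** Keep 312 and correct what section 2.12 says about it. Suggested text, with the power and the form of the test to be confirmed by the sponsor:

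> With a two-sided pooled Z test at alpha 0.05, 129 patients per group give 90% power to detect 56% versus 36%. If 312 patients are enrolled and 20% drop out, about 125 per group will have an observed six-month mRS, which gives about 89% power; 129 per group is reached if dropout does not exceed 17%.

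This costs one reworded passage and a slightly less favourable stated figure. Enrolment, design and analysis do not change, and the 312 in the abstract can stay.

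If the sponsor prefers to secure 129 per group at 20% dropout, the total becomes 324 (162 per group), which is 12 more patients, and the abstract must change with section 2.12.

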### Statistical analysis

2.13

Inferential statistical analyses as specified will be conducted, and all comparisons will be between the ABRS granule group and the placebo group. The statistical analyst will be blinded to the participants’ personal information and group assignment during the trial. The primary analysis will be based on the full dataset following the intention-to-treat analysis principle for all efficacy outcomes, while the secondary analysis will be based on the per protocol dataset. For the analysis of safety outcomes, a safety dataset will be used. The primary outcome will be determined by a comparison of the changes in the patients’ mRS scores between the 2 groups at 6 months after onset. The secondary outcomes will include the mortality rate, hematoma enlargement percentage, all-cause mortality rate, adverse events, TCM stroke syndrome evaluation scale score, BI, and NIHSS score. The hematoma enlargement percentage will be measured at baseline, 24, 48, and 72 hours after taking the medicine and 14 days after onset. The mortality rate, all-cause mortality rate, BI, and TCM stroke syndrome evaluation scale score will be measured at 14 days, 3 months, and 6 months after onset. The NIHSS score will be measured at 14 days after onset. The mRS score will be measured at 3 and 6 months after onset.

Missing data regarding the primary and secondary outcomes will be imputed using the last observation carried forward (LOCF) method. Independent *t* tests or Wilcoxon rank-sum tests will be used to analyze continuous outcomes. Chi-squared tests will be used to analyze categorical data. Analysis of variance or a generalized linear mixed model will be used for repeated measurement data. Regarding mortality, survival probabilities will be estimated using the Kaplan–Meier method. Two-sided 95% confidence intervals will be constructed for assessment, and a 2-sided alpha level of 0.05 will be used to indicate significance. Adjustments will be made for baseline imbalances. Descriptive statistics, including the number and percentage for categorical variables and the number, mean, standard deviation, median, minimum and maximum for continuous variables, will be provided. Listings of individual patient data will also be produced. A comprehensive statistical plan will be prepared and finalized prior to unblinding and analysis of the data.

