#### Primary outcome

2.9.1

The primary outcome will be the disability degree (mRS score) at 6 months after onset. The mRS is widely used to assess disability in stroke patients.^[14]^ The mRS divides the disability degree into 6 grades, and the score ranges from 0 to 5. A higher mRS score indicates a more serious degree of disability.

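### The primary endpoint is described in three incompatible ways, and the 129 per group belongs only to the one (a binary unfavorable-mRS rate) that is not named as an outcome

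*Protocol article*

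**What the plan says.** Three sections of the protocol article describe the primary endpoint.

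- **Section 2.9.1, Primary outcome:** "The primary outcome will be the disability degree (mRS score) at 6 months after onset". This is a score at one time point. The same section adds "The mRS divides the disability degree into 6 grades, and the score ranges from 0 to 5".
- **Section 2.12, Sample size:** a binary rate. From an earlier study, "the rate of unfavorable disability (according to the mRS score) in the control group was 56" per cent; the assumed value "in the treatment group will be 36%, that is, decreased by 20" percentage points. Then: "After a 2-sided Z test, PASS software calculated that the sample size of each group should be 129". Neither the mRS cut-off that makes disability unfavorable nor the power is given.
- **Section 2.13, Statistical analysis:** "The primary outcome will be determined by a comparison of the changes in the" mRS scores of the two groups at 6 months. The starting point of the change is not stated. The section assigns t or Wilcoxon tests to continuous outcomes and chi-squared tests to categorical ones, without saying which kind mRS is. It also says "a 2-sided alpha level of 0.05 will be used to indicate significance".

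The unfavorable proportion is not listed as a primary or secondary outcome anywhere outside section 2.12.

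**The concern.** A sample size is a statement about one test of one quantity. Here the quantity that produced 129 per group is not one that the protocol says it will test, and the quantity it says it will test has no planning assumption behind it: no mean difference, no standard deviation and no distribution over grades.

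Two things are at stake. First, a reader cannot tell what power the trial has for its declared primary comparison. Second, a proportion, a 6-month score and a change in score respond to different features of the data, so one version can be significant when another is not. Until the text settles on one, the protocol does not fix what a positive trial would mean.

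**Working it through.** **Step 1. Reproduce 129.** Inputs: 0.56 and 0.36, two-sided Z test (section 2.12); alpha 0.05 (section 2.13); 1:1 allocation (section 2.1). Power is not stated, so it was varied. For the pooled Z test without continuity correction:

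n = [1.960·√(2·p̄·(1−p̄)) + z_power·√(p₁(1−p₁) + p₂(1−p₂))]² / (p₁−p₂)², with p̄ = 0.46.

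At 90% power: [1.960·√0.4968 + 1.2816·√0.4768]² / 0.04 = (1.3815 + 0.8849)² / 0.04 = 128.4, so **129**. The same formula gives 97 at 80% power, 110 at 85% and 159 at 95%. The stated figure is therefore correct for the proportion, with 90% power implied.

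**Step 2. Try the same for a score.** The formula n = 2·(1.960 + 1.2816)²·SD²/d² needs a difference d and an SD, and the protocol gives neither. Assumed values show how wide the range is. With SD 1.5, 90% power needs 526, 296, 190, 132 or 97 per group for d = 0.3, 0.4, 0.5, 0.6 or 0.7. With 129 per group, power for those differences is 36%, 57%, 76%, 90% and 96%.

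**Step 3. Hold the protocol's own effect fixed.** Both scenarios below keep the drop from 56% to 36%. Assumptions not in the protocol: unfavorable means mRS 3 or more, and the control distribution over grades 0–5 is 8/18/18/22/22/12%.

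- *Proportional shift.* The odds ratio is (0.56/0.44)/(0.36/0.64) = 2.26. The treated distribution becomes about 16.4/27.8/19.7/17.5/12.9/5.7%. The mean difference is 0.68 and the SD 1.48. About 98 per group are needed, and power with 129 is 96%.
- *Effect only at the cut-off.* 20% of patients move from grade 3 to grade 2. The mean difference is 0.20 × 1 = 0.20 and the SD 1.49. About 1,174 per group are needed, and power with 129 is 19%.

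**Step 4. Check by simulation, 129 per group.** A second assumed control distribution includes death as grade 6: 6/16/22/17/17/7/15%. Its cut-off scenario moves 17% from grade 3 to 2 and 3% from grade 4 to 2.

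| Scenario | Binary Z test | t test on 6-month score | Rank test on 6-month score |
|---|---|---|---|
| Proportional shift, either distribution | about 90% | 95–96% | 96–97% |
| Effect at cut-off, grades 0–5 | about 90% | 19% | 21% |
| Effect at cut-off, grades 0–6 | about 90% | 17–18% | 25% |

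On the same simulated data, the binary test and the t test disagreed on significance in about 6–7% of trials under the proportional shift and about 72% when the effect sat at the cut-off.

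These runs use the 6-month score. A change score would also depend on its reference, which is not stated: section 2.3.1 requires a pre-onset mRS of 0–1, Table 1 schedules mRS at enrollment, and section 2.13 lists mRS only at 3 and 6 months.

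**The case against.** The strongest reply is that this is a condensed article. Section 2.13 promises a comprehensive statistical plan, finalized before unblinding and analysis, and an analyst blinded to group assignment. Listing tests by data type is ordinary in such an article. This stands against one tempting reading: a reader might infer that the choice among the three versions stays open until results are seen. The document does not support that. The reply does not remove the contradiction, because the protocol makes three statements about one endpoint and a later plan would have to override at least one of them.

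A second reply is that score-based analyses of mRS are often at least as powerful as a dichotomy, so the trial loses nothing. That is true under a proportional shift and false when the effect lies at the cut-off, where the dichotomy is far more powerful. The cut-off scenario is a deliberate extreme. Together the two show only that the direction is unknown. A reader should infer neither that the trial is underpowered nor that it was sized on the weaker test.

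A third reply concerns the change score. It is tempting to criticize it as a change from an acute-phase value, but no section says which score it is measured from.

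**Conclusion.** The point holds as an inconsistency within the protocol. Sections 2.9.1, 2.12 and 2.13 name a 6-month score, an unfavorable rate and a change in score, and 129 per group is derived only for the rate. This part rests on the document's own figures plus an inferred 90% power.

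The consequence for power is unknown rather than adverse: about 95–97% or about 17–25% for a score comparison, depending on where on the scale the same 20-point drop arises. Those ranges rest on assumed grade distributions and an assumed cut-off of mRS 3 or more. They show that the versions can disagree; they do not predict this trial. Because the contradiction concerns the primary conclusion, it should be resolved before unblinding.

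**What to change.** Reconcile sections 2.9.1, 2.12 and 2.13 to one primary endpoint and one test.

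**Simplest option: the endpoint that was sized.** Make the primary the proportion with unfavorable disability at 6 months. State the mRS cut-off, and count death as unfavorable, since the 0–5 scale in section 2.9.1 gives death no score. Use a two-proportion comparison, preferably adjusted for the randomization strata (center and time of enrollment). This keeps 129 per group; state the 90% power. The 6-month mRS score or ordinal shift becomes supportive, and the change score is no longer the primary comparison.

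**If the sponsor keeps a score or ordinal primary:** section 2.12 should say that 129 was derived for the binary endpoint, and should restate the power for the chosen test from a stated effect or grade distribution. Whether the number of patients still suffices is then open until that calculation is done.

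**Cost.** The first option needs no additional patients or visits, but it formally rewords the primary outcome and must be documented as an amendment before unblinding. A binary primary also uses less of the scale than an ordinal one.
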